### Operators

Operators will be two final-year undergraduate dental students and one specialist in pediatric dentistry with 3 years of experience treating children. They were trained in both treatments. Training comprised a lecture on ART and the HT by clinicians experienced in the treatments and experienced in clinical trials. Also, the undergraduate students participated in a hands-on laboratory-based workshop for the handling and application of the materials and practicing carrying out both ART and the HT by clinicians experienced in the treatments. All operators will also undergo 2 weeks of training with children, using the different techniques before starting the study. This phase will be carried out in the field setting with similar children to those participating in the study, under the direct supervision of clinicians experienced in ART and HT.

Each child will be allocated to be treated by one of the operators with the aid of the random allocation list. All treatments will be performed on the school premises, in field conditions without the use of dental chair or other facilities from a clinical environment.

### Protocols for interventions

#### Control arm – Atraumatic Restorative Treatment (ART)

The teeth will be prepared according to the ART approach proposed by Frencken et al. [3], and no local anesthesia will be used as per standard ART protocol. The cavities will be filled according to Yu et al. [14] (Table 1).

**Table 1 Tab1:** Protocol for Atraumatic Restorative Treatment (ART) restorations: preparing the teeth according to Frencken et al. [3] and restoration of cavities according to Yu et al. [14]

1. Preparing the cavity • Place cotton wool rolls alongside the tooth to be treated. • Remove plaque from tooth surface with wet cotton wool pellets. • Dry the tooth surface with dry cotton wool pellets. • If necessary, make the entrance of the cavity wider with a dental hatchet. • Remove the carious dentine with excavators, until the enamel-dentine junction is caries free. • Fracture off unsupported thin enamel with the hatchet. • Clean the cavity with wet and then dry with cotton wool pellets. • Remove the caries near the pulp carefully. In this area only the completely soft and demineralized tissue must be removed. • Clean the cavity again with wet cotton wool pellets. • Complete the procedure by drying the cavity with dry cotton wool pellets. • Place a matrix strip between the teeth. This matrix must be pre-curved. Insert a wedge to support the strip under the contact point at the gum margin. Advise the child that he/she might feel a little uncomfortable during this procedure. 2*.* Conditioning the cavity • Apply one drop of GC Cavity Conditioner liquid (GC Europe, Leuven, Belgium) on paper pad. • Dip a cotton wool pellet in clean water. • Remove excess of water from the cotton wool pellet by lightly touching against a dry cotton wool roll, tissue or gauze. • Dip the moist cotton wool pellet in the GC Cavity Conditioner liquid. • Condition the cavity and adjacent fissures with the liquid for 10–15 seconds. • Wash the cavity and fissures immediately with three sequences of cotton wool pellets, dipped in clean water. • Dry the cavity with three sequences of dry cotton wool pellets. 3. Restoring the cavity • Ensure that the tooth is kept dry during the restoration phase • The capsule of EQUIA Forte, capsules (GC Europe, Leuven, Belgium) should be activated and mixed. Before activation, shake the capsule or tap its side on a hard surface to loosen the powder. To activate the capsule, push the plunger until it is flush with the main body. Immediately place the capsule into a metal capsule applier and click the lever once and it will be activated. Immediately remove the capsule and set it into a mixer (or an amalgamator) and mix for 10 seconds • Remove the capsule from mixer and place into a metal capsule applier again. Make two clicks to prime the capsule. Within 10 seconds maximum after mixing, start to extrude the mixture directly into the preparation. Extra care should be taken to avoid moisture contamination or drying out • Place the index finger on the restorative material, press and remove finger sideways after a few seconds • Remove visible excess of glass ionomer cement (GIC) with a medium or large excavator • Wait 1–2 minutes till the material feels hard, whilst keeping the tooth dry • Remove matrix turning this to the other side (adjacent tooth) and wedge carefully and check the bite using articulation paper and adjust the height of the restoration with the applier/carver if needed • Using a micro-tip applicator, apply G-Coat Plus (GC Europe, Leuven, Belgium) to the occlusal and proximal surface of restoration. A new metallic matrix band and wedge must be applied and light cured for 20 seconds at occlusal, 20 seconds at buccal and 20 seconds at the lingual surface. G-Coat Plus is indicated to seal and protect the surface of glass ionomer • Remove the matrix, wedge and cotton wool rolls • Child will be told not to eat for at least 1 hour after the treatment. A sticker with the time at which they are allowed to eat again will be pasted on their t-shirt	

#### Intervention Arm – Hall Technique (HT)

The treatments will be carried out according to the HT protocol of Innes et al. [27]. No local anesthesia will be used as it is not required (no dentine is removed) and as per standard HT (Table 2).

**Table 2 Tab2:** Protocol for carrying out Hall Technique restorations, following the Innes et al. [27] protocol

First visit: • Assess the tooth shape, contact points/areas and the occlusion. • Use orthodontic separators to create space for fitting a Hall crown, unless there are no contact points. In order to protect the airway, the child will be sat upright • Thread two lengths of dental floss through the separator. Stretch the separator and floss taught and floss through the contact point briskly and firmly until the leading edge only is felt “popping through” the contact point. Remove the floss and make a second appointment with the patient 3 to 5 days later. Second visit: • Remove the separator with an excavator. • Gently remove loose plaque and food debris only from the cavity. • Assess the occlusion: measure the patient’s occlusal-vertical dimensions (OVD) with a millimeter probe using the distance between the most coronal points of the primary canines in order to assess the degree of overbite after mounting of the crown. • Protect the airway by placing a gauze swab square between the tongue and the tooth to be crowned. • Select the correct crown size (Stainless Steel Crowns, 3 M™ ESPE™, St. Paul, MN, USA). The crown should covers all the cusps and approaches the contact points, with a slight feeling of “spring back.” You should aim to fit the smallest size of crown which will seat. • Keep the treatment area free from saliva by isolating the tooth with cotton wool rolls. • Dry the inside of the crown with dry cotton pellets. • Mix the encapsulated glass ionomer cement (GIC) (Fuji I, GC Europe, Leuven, Belgium) for 10 seconds, according to the manufacturer’s instructions. • Load the crown generously with GIC (at least two thirds full). Avoid air blows and voids. • Place the crown over the tooth and seat the crown into place by finger pressure or ask the child to bite it into place. • Check the crown position as soon the crown is fitted. • Wipe away the excess GIC with a cotton wool roll or the gauze swab used to protect the airway. • Place a cotton wool roll between the crown and the opposing tooth and ask the child to bite firmly on the crown for another 2–3 minutes. • Remove excess cement, flossing between the contacts. • Blanching usually disappears within minutes. The occlusal discrepancy should resolve in a few weeks. • Measure the degree of bite opening and record in the notes. If excessive, then consider removing the entire crown. • Check the buccal relationship of the crowned tooth with its opposing number. If there is a displacing contact, resulting in a cross bite, then manage as for excessive bite propping.	

### Data analyses

Outcome data for the trial will be analyzed as intention-to-treat (ITT) so that all participants randomized and all events will be accounted for in the primary analysis. However, if (1) more than 10 % of children cannot tolerate either one or both of the treatments at the time of treatment, or (2) there is a difference greater than 20% in the dropouts between the arms (therefore raising the index of suspicion that there is a problem with tolerance of the treatments or other problem with delivery), we will also carry out an “on treatment” (also known as per-protocol) analysis and interpret the differences between ITT and “on treatment” appropriately.

### Primary outcome evaluation

One trained and calibrated examiner will carry out the follow-up evaluations. The examiner will undergo a training period according to the criteria adopted and in order to calculate intra-observer reliability, 20 % of the sample evaluated at the first evaluation period will be re-evaluated after 2 weeks. The intra agreement will be calculated and score above 0.7 will be accepted.

The treatments will be classified as “success” when they present as clinically satisfactory (that is where there have been no failures). Failures will be scored as “Minor Failures” and “Major Failures” (adapted from Innes et al., [21]). The Minor Failures will be those in which there is a defect in the restoration/crown, but it does not interfere with the tooth health. The Major Failures are when there are signs or symptoms of irreversible pulp damage, such as dental fistula/abscess, tooth fracture or failures that cannot be repaired (Table 3).

**Table 3 Tab3:** Evaluation criteria for the assessment of treatments (modified from Innes et al. [21])

Success	• satisfactory restoration/crown, no intervention required • no clinical signs or symptoms of pulp pathology • tooth exfoliated
Minor Failures	• secondary caries, or new lesions detected clinically • crown presents perforation • restoration fracture or wear - intervention required • loss of restoration - tooth that can be re-restored • crown loss - tooth able to be re-treated • reversible pulpitis, which could be treated without the need for extraction or pulpotomy
Major Failures	• irreversible pulpitis or dental fistula/abscess, requiring pulpotomy or extraction • loss of restoration/crown - tooth does not capable of being re-restored

The primary outcome of survival rate will be analyzed primarily as a composite of Minor and Major Failures but we will also conduct a further analysis by dividing the outcomes into two levels: assessment of treatment survival (Minor Failure) and tooth survival (Major Failure).

#### Treatment (restoration) survival

ART restorations and HT scored as satisfactory will be considered “successful,” while those presented Minor and/or Major Failures will be considered as “failed.”

#### Tooth survival

Treatments will be considered as being “successful” for teeth where treatments are scored as satisfactory or where there has been Minor Failures. Teeth that present Major Failures will be considered as “failure for tooth.”

### Secondary outcomes evaluation

For the assessment of discomfort, the Wong-Baker FACES pain rating scale, an ordinal six-point scale ranging from 0 to 5, will be used [28]. A score of 0 shows a smiling face, indicating no discomfort, whereas a score of 5 shows a crying and sad face, indicating great discomfort. This method has been validated for the assessment of pain and discomfort in children, before and after treatments [28, 29].

To evaluate the perception and concerns related to dental appearance, the Child’s and Parent’s Questionnaire about Teeth Appearance [30] will be used and applied through an interview with children in the school, as well as being filled out by their parents/caregivers at home. This instrument has a version for children and a version for their parents, including questions related to physical, psychological and social order, beyond the perceptions of color change and other esthetic conditions related to the child’s teeth. The questionnaire has five questions with the first three items assessing how the child felt uncomfortable (physical domain of the concept of health), concerned (psychological domain) and avoided smiling (social field) due to the appearance of his/her teeth. An additional item with four sub-items assesses the perception of children and their parents/caregivers about the appearance, color and health of teeth and the last item assesses the opinion of children and their parents/caregivers regarding the satisfaction with the teeth color.

The questionnaire for the evaluation of acceptance in relation to treatment carried out will be applied through interview with children in the school as well as being filled out by their parents/caregivers at home. These questionnaires are based on questionnaires used by Bell et al. [31]. They were rewritten in order to be useful for both the ART and the HT (see Additional file 2). A dentist who is fluent in both languages translated the questionnaires from English to Portuguese. The questionnaire for the children contains six items and employs a five-point pictorial Likert scale. The possible responses are: strongly agree, agree, indifferent, disagree and strongly disagree. The parental questionnaire has five questions with the same possible responses.

The assessment of the OVD will be performed according to a modified version of van der Zee and van Amerongen [32]. Ideally, this will be measured using the canines on the same side of the jaw as that where the treatment takes place. If this is not possible we will measure the OVD on the contralateral side of the jaw. If there are no canines present, we will measure the OVD using the first primary molars. The OVD measurement and the teeth measured will be recorded. One examiner will measure the OVD before and after the treatment, and in the subsequent evaluations. The examiner will be trained and calibrated according to the protocol adopted for this measurement. The OVD will be measured using a probe with markings at 1, 3, 6 and 9 mm. The distance from the lowest point of the gingiva, around the lower canine on the vestibular side up to the point where the tip of the upper canine ends, will be measured. This tip does not have to be directly above the lowest point in the gingiva around the lower canine as an imaginary line will be being drawn through the tip of the antagonist and the distance measured from the gingiva to the line (Fig. 2).

**Fig. 2 Fig2:**
[figure not shown]
Method for measuring occlusal-vertical dimension (OVD) using a probe with markings at 1, 3, 6, and 9 mm

Plaque [33] and gingival bleeding indices [34] will be recorded on the treated tooth as well as obtained by averaging the measurements from seven index teeth [22] (Table 4).

**Table 4 Tab4:** Evaluation criteria for the assessment of plaque index [33] and gingival health [34]

Plaque index scores [33]	• 0: no plaque • 1: thin visible plaque, difficult to identify • 2: thick visible plaque, easily detected.
Gingival health scores [34]	• 0: Normal: the gingival tissue appears firm, with pinkish or pale pink and opaque surface, with thin margins and variable degree of stippling. Contact with millimeter probe show its firmness • 1: slight inflammation: the gingival margin has slight change of color (reddish or bluish red) and is slightly swollen. Does not bleed after gentle probing • 2: moderate inflammation: the gingival tissue has become swollen (rounded edge, or bright red/blue). There is bleeding after gentle probing; 3: severe inflammation: the gingival tissue has markedly red or bluish red, swollen and enlarged, with ulcerations. Tendency to spontaneous bleeding

For the assessment of changes in DMFT/dmft, the same criteria for the evaluation of caries presence used at the baseline evaluation will be used [25] and the DMFT and dmft will be recorded [26].

An incremental cost-effectiveness ratio (ICER) will be calculated. The average cost per treatment will be quantified for both ART and the HT. Effectiveness will be measured by percentage of treatment survival. A microcosting will be carried out to estimate the direct costs of treating children with ART or the HT. This will include the capital costs of all equipment and instruments, materials and overheads, and the costs of time and labor. Additionally, the procedures will be timed using a stopwatch, started when the child has his/her mouth open and the operator is about to start the restorative intervention and stopped when the child stands up from the treatment table. The initial cost of treatments will be calculated, taking into account the parameters described in the Table 5. Therefore, the initial costs of treatments will be calculated by summing the expenses of capital cost, material cost and labor cost [35]. The ICER will be generated per treatment group by dividing the average initial cost by the survival after 3 years:

**Table 5 Tab5:** Parameters used to calculate the costs per treatment

Capital cost	• Fixed cost of equipment and instruments such as the cost of autoclave and examination kits. For analysis we will assume that the lifespan of a dental instrument is approximately 3 years or 1095 days (constant depreciation rate).
Materials cost	• supplies such as gloves, masks, articulating paper, restorative material and PMCs. Their accumulated costs will be estimated per restoration.
Labor costs	• salaries of dentists and dental nurses delivering treatment will be calculated using the top point in their Brazilian Public health Service salary scales for the city in which the treatment is being provided. The labor cost per day will be divided by the number of restorations/ PMCs placed per day.

$$ ICER=\left({\mathrm{cost}}_i\hbox{-} {\mathrm{effectiveness}}_i\right)/\left({\mathrm{cost}}_c\hbox{-} {\mathrm{effectiveness}}_c\right)\;\mathrm{where}\;i=\mathrm{intervention}\;\mathrm{and}\;c=\mathrm{control}. $$

The perceptions of parents and children regarding the OHRQoL will be evaluated using the Child Perceptions Questionnaire (CPQ). This questionnaire takes into account the cognitive abilities and lifestyles, and is validated for Brazilian children aged from 8 to 10 years (CPQ_8–10_) [36, 37]. The instrument consists of 29 questions, distributed into four domains (child symptoms, function, psychological, and self-image/social interaction domains) and in a family impact section (oral symptoms, functional limitations, emotional well-being and social well-being). Answers will be recorded through a Likert scale from 0 to 4: 0 = never, 1 = once or twice, 2 = sometimes, 3 = often, 4 = very often. The minimum possible score is 0, the maximum possible score is 116, with higher scores indicating a greater negative impact on OHRQoL. The CPQ_8–10_ questionnaires will be applied as an interview to children in the school. Furthermore, the parents will also be invited to answer the Brazilian version of the Parental-Caregiver Perceptions Questionnaire (P-CPQ) at home [38]. The questionnaire is composed of 35 questions that assess the perceptions of parents and/or guardians regarding the impact of oral diseases on the quality of life of children aged 6 to 14 years as well as a rating scale consisting of 14 questions that assess the effects of oral disorders in family functioning. Questions 1 and 2 refer to the overall perception of those responsible for oral health and the child’s overall well-being. Answers will be recorded using a Likert scale from 0 to 4: 0 = excellent, 1 = very good, 2 = good, 3 = fair, 4 = bad. The remaining questions are divided into four broad categories: oral symptoms (questions 3–8), functional limitations (questions 9–16), emotional well-being (issues 17–24) and social welfare (questions 25–35). Questions 36–49 refer to the impacts of oral disorders in family welfare. Response options range from 0 to 5: 0 = never, 1 = once or twice, 2 = sometimes, 3 = often, 4 = every day or almost every day; 5 = do not know. The total score is obtained by summing the scores of all issues. Higher scores indicate greater the impact of oral diseases on the quality of life.

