**Methods/Design:**

This two-arm, parallel group, patient-randomized controlled, superiority trial will have treatment provided in schools. Schoolchildren (*n* = 124, age 6–8) with at least one occluso-proximal carious primary molar lesion will have random allocation to treatment with ART or HT. Baseline measures and outcome data will be assessed through participant report, clinical examination and parent report/questionnaires. The primary outcome is survival rate, a composite measure of absence of Minor Failures (a defect in the restoration/crown, but not interfering with tooth health) and Major Failures (signs or symptoms of irreversible pulp damage, such as dental fistula/abscess, tooth fracture or failures that cannot be repaired). Secondary outcomes are: (1) child-reported discomfort, (2) childrens’ and (3) parents’ concerns around dental appearance and (4) acceptability of treatments, (5) occlusal-vertical dimensions (OVD) changes, (6) plaque index, (7) gingival health, (8) decayed, missing, filled teeth in permanent teeth (DMFT)/decayed, missing, filled teeth in primary teeth (dmft), (9) oral health-related-quality of life, reported by children and parents/caregivers, (10) the incremental cost-effectiveness, and (11) operator effect. A trained and calibrated examiner will evaluate the treated teeth after 1 week, then 1, 6, 12, 24 and 36 months post treatment. Kaplan-Meier and Cox regression tests will be used to investigate the primary outcome. The Mann-Whitney or *t* test, Friedman test, paired *t* test or Wilcoxon test and Ordinal Logistic Regression Analysis will be used to analyze the secondary outcomes.

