#### Secondary outcomes

The Kolmogorov-Smirnov and Levene tests will be used to consider the normality distribution and homoscedasticity of the data, respectively. Depending on the data distribution, the Mann-Whitney test or *t* test will be applied to compare the degrees of discomfort, perception and concerns related to dental appearance reported by the child and their parents/caregivers; the child and their parent/caregivers’ reported acceptance of treatments among the two groups of intervention, as well as to evaluate the difference in mean scores of CPQ and P-CPQ among the two groups of intervention. The differences between the mean scores of the responses from the CPQ and P-CPQ questionnaire obtained at 1 month and at baseline will be calculated and tested, using a paired *t* test. The Friedman test will be used to compare the changes with regards to concerns related to dental appearance reported by the child and their parents/caregivers, changes in OVD; plaque index and gingival health. To evaluate the association between the secondary outcomes and children variables Ordinal Logistic Regression Analysis will be used. For cost-effectiveness analysis, the primary measure will be the survival rate of treatments. Therefore, as previously mentioned, the ICER will be generated per treatment group by dividing the average initial cost by the survival after 3 years:$$ ICER=\left({\mathrm{cost}}_i-{\mathrm{effectiveness}}_i\right)/\left({\mathrm{cost}}_c-{\mathrm{effectiveness}}_c\right)\mathrm{where}\;i=\mathrm{intervention}\ \mathrm{and}\;c=\mathrm{control}. $$

The significance level for all analyses will be *p* <0.05.

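### The incremental cost-effectiveness ratio is misdefined in both places where it is stated: neither the sentence nor the formula gives difference in cost over difference in survival

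*Protocol article*

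**What the plan says.** The abstract of the protocol article (Methods/Design) lists among the secondary outcomes "10) the incremental cost-effectiveness, and (11) operator effect". The section Secondary outcomes evaluation commits to the measure by name: "An incremental cost-effectiveness ratio (ICER) will be calculated". It names both inputs. On cost: "The average cost per treatment will be quantified for both ART and the HT". On effect: "Effectiveness will be measured by percentage of treatment survival".

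It then gives the rule in words: "The ICER will be generated per treatment group by dividing the average initial cost by the survival after 3 years". The same rule is repeated under Statistical analysis, Secondary outcomes.

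Each time, the sentence introduces a formula, with i for intervention and c for control. After Table 5 the terms for each arm are joined by a dash coded as a text hyphen: "cost}}_i\hbox{-} {\mathrm{effectiveness}}_i". Under Statistical analysis the dash is a plain minus: "ICER=\left({\mathrm{cost}}_i-{\mathrm{effectiveness}}_i\right)/\left({\mathrm{cost}}_c-{\mathrm{effectiveness}}_c". No other section states a different rule.

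**The concern.** An ICER is a single number for the contrast between two treatments: the extra cost divided by the extra effect. The article gives two rules under that name, and neither is of this form.

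- The sentence produces two numbers, each arm's cost over its own survival. These are average cost-effectiveness ratios.
- The formula, read literally, takes a survival figure away from a sum of money in each arm and then divides the arms. Quantities in different units are being subtracted, so the answer changes with the unit chosen for either one.

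At stake is a named secondary outcome that the Discussion links to public health policy. A policy-maker needs the price of one more surviving treatment if HT replaces ART, and neither rule gives it. Because the two rules also differ from each other on the literal reading, an analyst would have to choose between them, or depart from both, once costs and survival are known.

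**Working it through.** **Inputs.** The article gives no cost and no ICER figure, so there is no stated result to reproduce.

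- Survival: Sample size calculation gives 62% for ART at 2 years and an absolute difference of 25 percentage points. Assuming the difference favours HT, HT survival is 62 + 25 = 87%. These are 2-year planning values standing in for the unknown 3-year values.
- Costs: assumed, in arbitrary currency units, at several levels.

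**Rules compared** (C = mean cost, E = survival):

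- Standard ICER: (C_HT − C_ART)/(E_HT − E_ART)
- Sentence: C/E in each arm
- Formula, literal: (C_HT − E_HT)/(C_ART − E_ART)
- Formula with the dash as a hyphen, taken as a ratio of the arms' C/E: (C_HT/E_HT)/(C_ART/E_ART)

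**Case 1: HT 20, ART 10.**

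- Standard: (20 − 10)/(0.87 − 0.62) = 10/0.25 = 40 per extra surviving treatment
- Sentence: 20/0.87 = 22.99 for HT; 10/0.62 = 16.13 for ART
- Literal formula, proportion: (20 − 0.87)/(10 − 0.62) = 19.13/9.38 = 2.04
- Literal formula, percentage: (20 − 87)/(10 − 62) = −67/−52 = 1.29
- Hyphen reading: 22.99/16.13 = 1.43

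**Case 2: HT 10, ART 20.** HT is cheaper and better, so it dominates.

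- Standard: (10 − 20)/0.25 = −40, to be reported as dominance
- Sentence: 10/0.87 = 11.49 for HT; 20/0.62 = 32.26 for ART
- Literal formula, proportion: (10 − 0.87)/(20 − 0.62) = 9.13/19.38 = 0.47
- Literal formula, percentage: (10 − 87)/(20 − 62) = −77/−42 = 1.83
- Hyphen reading: 11.49/32.26 = 0.36

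The same data fall on opposite sides of 1 depending only on how survival is entered. The percentage, which gives 1.83, is the scale that the article names for effectiveness.

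**Other cost pairs.**

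| Cost HT / ART | Standard ICER (proportion) | Literal, proportion | Literal, percentage | Hyphen reading |
|---|---|---|---|---|
| 30 / 20 | 40 | 1.503 | 1.357 | 1.069 |
| 20 / 20 | 0 | 0.987 | 1.595 | 0.713 |
| 20 / 30 | −40 (HT dominates) | 0.651 | 2.094 | 0.475 |
| 300 / 200 | 400 | 1.500 | 1.543 | 1.069 |

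The first and last rows hold the same costs in a currency ten times smaller. The ICER rises tenfold, as it should. The literal formula in percentages moves from 1.357 to 1.543, which corresponds to no change in the treatments.

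**The case against.** **The dash may be a hyphen.** After Table 5 it is coded as a text hyphen. Read as the words cost-effectiveness, the formula would follow from the sentence before it: form cost over survival in each arm, then compare intervention with control. This reading is possible, so the subtraction cannot be taken as certain. Against it, the version under Statistical analysis has a minus, and cost and effectiveness carry separate subscripts in both places. Even if the hyphen was meant, the result is a ratio of two average ratios, so the definition is still wrong.

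**The outcome may seem impossible to produce.** A reader might infer this, but the article does not support it. Mean cost per arm and 3-year survival per arm are both planned, and the standard ICER needs nothing else. The rule is wrong; the data are sufficient.

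**Everything reported may seem to lack a meaningful unit.** That is also too strong. Cost over survival in one arm is money per surviving treatment, which is interpretable and merely mislabelled. The Discussion shows some interest in it, since it speaks of cost relative to survival for each arm. The unit problem belongs only to the formula read literally.

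**A value of 0.47 still points towards HT.** True: on the proportion scale, Case 2 loses meaning without reversing direction. The crossing of 1 appears when survival is entered as a percentage.

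**Such detail may belong in an analysis plan.** This is not an omission. The article states the rule twice, once in its statistical analysis section, and states it wrongly both times.

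**It is one of eleven secondary outcomes.** This stands. No hypothesis test, sample size or data collection depends on it, which limits the severity.

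**Conclusion.** The point holds as a definitional error in secondary outcome 10. The article promises an incremental ratio and nowhere defines one. The sentence gives average ratios, and the formula gives either a unit-dependent quantity or a ratio of average ratios.

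The error itself rests on no assumption. Its illustrated size does: the costs are invented, the survivals are 2-year planning values rather than 3-year results, and the direction of the 25-point difference is assumed. The 40 is therefore not a forecast. What carries over to other inputs is that the literal formula responds to units and that none of the stated rules returns extra cost per extra surviving treatment.

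The primary survival analysis is unaffected. This is a should-fix: a wrong rule for a named outcome, easily put right with data already planned.

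**What to change.** In both places (Secondary outcomes evaluation, and Statistical analysis, Secondary outcomes), replace the sentence and the formula with:

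ICER = (mean cost_HT − mean cost_ART) / (3-year survival_HT − 3-year survival_ART)

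State whether survival enters as a proportion or in percentage points, so that the unit is explicit: in the 30/20 example, 40 per extra surviving treatment equals 0.40 per percentage point. State that dominance is reported when one arm is both cheaper and better, instead of a negative ratio. If cost over survival per arm is kept, label it an average cost-effectiveness ratio.

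The cost is one corrected sentence and one corrected formula, each made twice. No new data or procedures are needed. The correction is best dated before costs and 3-year survival are compared by arm.
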